### 2.2. Study outcomes

The primary outcome of the trial is the relative change from baseline in peanut-specific/total IgE ratio at the end of the treatment phase (week 24). The use of the specific/total IgE ratio aims to control for non-specific fluctuations in IgE production.

Secondary outcomes include the following:

The relative change in peanut-specific IgG4/IgE (sIgG4/sIgE) ratio from baseline to week 24.The absolute change in peanut sIgG4 from baseline to week 24.The maximum period of avoidance after which an OFC with 300 mg peanut protein is still tolerated.The mean cumulative function of food dosing allergic reactions.The highest tolerated dose on week 36 OFC.The time from the onset of OIT to the maintenance dose of 300 mg.The overall rate of adverse events (AEs).

Exploratory outcomes include the following:

a. Change in peanut atopy patch test from baseline to weeks 12, 24, and 48.b. Change in peanut skin test from baseline to weeks 12, 24, and 48.c. Relative change in peanut-specific/total IgE from baseline to weeks 2, 6, 12, 36, and 48.d. Relative change in peanut sIgG4/sIgE ratio from baseline to weeks 2, 6, 12, 36, and 48.e. Absolute change from baseline in peanut sIgG4 to weeks 2, 6, 12, 36, and 48.f. The highest tolerated dose on week 38 OFC [72 h SU].g. The highest tolerated dose on week 40 OFC [1-week SU].h. The highest tolerated dose on week 43 OFC [2-week SU].i. The highest tolerated dose on week 48 OFC [4-week SU].

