### 2.3. Selection of participants

The study aims to enroll 14 participants aged 14–50 years with serum peanut sIgE >50 kU/L. The inclusion and exclusion criteria are presented in Tables 1, 2, respectively. For female participants of child-bearing potential, a urine pregnancy test will be conducted on randomization day. Since asthma is an important concern when initiating OIT, a focus on uncontrolled asthma should be made. Criteria for uncontrolled asthma are as follows:

- History of two or more systemic corticosteroid courses within 6 months of screening or 1 course of systemic corticosteroids within 3 months of screening to treat asthma/wheezing;- One hospitalization or emergency department visit for asthma/wheezing within 6 months of screening;- Forced expiratory volume in 1 s (FEV1) <80% of predicted or FEV1/forced vital capacity (FVC) <75%, with or without controller medications;- Inhaled corticosteroid dosing of >500 mcg daily fluticasone (or equivalent).

**Table 1 T1:** Inclusion criteria.

1. Male or female participants 14–50 years old at screening visit.
2. History of IgE-mediated allergy to peanut protein.
3. Peanut-specific IgE level >50 kU/L.
4. Total IgE level <5,000 kU/L.
5. Willing to comply with all study requirements during participation in the study.
6. Signed informed consent and assent.

**Table 2 T2:** Exclusion criteria.

1. Previous adverse reactions to abatacept.
2. Known hypersensitivity to abatacept or any of its components.
3. Patients at risk of sepsis, such as immunocompromised or HIV positive.
4. Patient undergoing treatment with any other biologic agent.
5. Partly controlled or uncontrolled asthma, as defined by GINA 2020.
6. Unstable angina, significant arrhythmia, uncontrolled hypertension, chronic sinusitis, or other chronic or immunological diseases that, in the judgment of the investigator, might interfere with the evaluation, administration of the test drug, or pose additional risk to the subject (e.g., gastrointestinal or gastroesophageal disease, chronic infections, scleroderma, hepatic and gallbladder disease, and chronic non-allergic pulmonary disease).
7. Current users of oral, intramuscular, or intravenous corticosteroids, tricyclic antidepressants, or beta-blocker.
8. Concurrent/prior use of immunomodulatory therapy (within 6 months), including allergen-specific immunotherapy.
9. A diagnosis of eosinophilic esophagitis, eosinophilic colitis, or eosinophilic gastritis.
10. Pregnant or breastfeeding women.

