### 2.9. Statistical considerations

Based on observations from preclinical studies in mice, abatacept is expected to suppress the allergen-specific IgE surge induced by OIT. The relative change in specific/total IgE at 24 weeks will be compared between the two groups using Student's *t*-test. A 50% suppression was deemed clinically significant.

Based on the PALISADE trial (6), we expect the placebo group (OIT alone) to increase their specific IgE levels by 100% with a standard deviation of <30%. Based on this assumption, a sample size of 12 participants with a 1:1 randomization ratio would allow the detection of a 50% difference in the increase in sIgE, with an alpha risk of 0.05 and a power of 80%. A total sample size of 14 patients would allow to account for 15% of lost follow-up.

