### 3.1. On the choice of proxy outcome

ATARI is intended as a proof-of-concept study and will likely not be powered to detect differences in clinical remission. Its primary aim is, therefore, to assess differences in a proxy outcome that would be associated with the development of clinical remission.

Based on the choice of proxy outcome, we observed from preclinical studies that abatacept suppresses the initial surge in sIgE with allergen exposure (32). This is assumed to be the consequence of the suppression of peanut sIgE-producing plasma cells and T-cell reactivation and is shown to correlate with the likelihood of clinical remission (9, 17, 18). If this key finding cannot be replicated in humans, it appears reasonable to assume that the likelihood of replicating the clinical effects would also be low.

One risk of using the surge in sIgE as a primary outcome in such a small sample is that we are highly vulnerable to random non-specific variations in total IgE productions, which could have a confounding effect and decrease power. In our own experience of longitudinal testing during peanut OIT or epicutaneous immunotherapy, spontaneous variations in sIgE, even large, are non-clinically significant when they parallel variations in total IgE, hence the choice to measure changes in the sIgE over total IgE ratio as the primary outcome.

Changes in the sIgG4/sIgE ratio are another paraclinical outcome that is often measured during OIT. Since IgG4 production follows the same non-specific expansion/contraction variations as IgE, it is generally a more reliable measure of longitudinal changes in OIT than sIgE alone. However, it is unclear how abatacept will affect sIgG4 production. Based on preclinical data, it is possible that it may suppress the rise in sIgG4, which would complicate interpretation. The sIgG4/sIgE ratio will, therefore, be treated as a secondary outcome.

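### The 80% power in section 2.9 is worked out for sIgE, but the primary endpoint and its t-test use the sIgE/total IgE ratio, for which no power is shown

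*Protocol article*

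**What the plan says.** Section 2.2 defines the endpoint: "The primary outcome of the trial is the relative change from baseline in peanut-specific/total IgE ratio at the end of the treatment phase" (week 24). Section 2.9 plans the test on the same variable: "The relative change in specific/total IgE at 24 weeks will be compared between the two groups using" a Student's t-test.

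The sample-size paragraph of section 2.9 then changes variable. For the control arm, "we expect the placebo group (OIT alone) to increase their specific IgE levels by 100% with a standard deviation of <30" per cent. Twelve participants, 1:1, "would allow the detection of a 50% difference in the increase in sIgE" at alpha 0.05 and 80% power, and the total is raised to 14 for losses. The relevance threshold, "A 50% suppression was deemed clinically significant", is not tied to either variable.

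Section 3.1 explains the ratio as a way to remove fluctuation that sIgE shares with total IgE, "hence the choice to measure changes in the sIgE over total IgE ratio as the primary outcome". That reasoning is not carried into the calculation. Table 1 requires sIgE above 50 kU/L and "Total IgE level <5,000 kU/L". It sets no limit on the ratio itself.

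**The concern.** A power statement belongs to the variable whose mean, SD and effect went into it. Here all three describe sIgE, while the test will be run on sIgE divided by total IgE. The two are not interchangeable, because the numerator is contained in the denominator: when sIgE rises, total IgE rises with it, by an amount that depends on the participant's baseline share of peanut-specific IgE. The same surge therefore gives different ratio changes in different participants, and the denominator adds variation of its own.

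Section 3.2 says the trial is to inform a go/no-go decision on a larger trial. Whoever reads a null result will want to know what chance the primary test had of detecting the planned effect, and section 2.9 does not answer that for the variable tested.

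**Working it through.** **Inputs.** From section 2.9: sIgE increase of 100% in the control arm, so 50% with abatacept for a 50-point difference; SD 30 points (the upper limit of what is stated); alpha 0.05, taken as two-sided; 6 evaluable per arm. From Table 1: baseline share f = sIgE/total IgE above 50/5,000 = 1%. The documents give no other information on f, so every range below is an assumption. The algebra treats sIgE and total IgE as measured in the same units.

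**1. The plan's own figure.** n per arm = 2 × (1.96 + 0.84)² × 30² / 50² = 5.6, so 6 per arm and 12 in total. Power by the normal approximation at 6 per arm is 82.3%. The figure reproduces, for sIgE. The planned t-test at 6 per arm and SD 30 has 74.0% power (80% needs an SD of about 27.8 or less), so 74% is the reference below.

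**2. The same effect on the ratio.** If sIgE changes by a factor s and other IgE is unchanged, the ratio changes by a factor s / (1 + f(s − 1)). With s = 2.0 and s = 1.5:

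| Baseline share f | Control | Abatacept | Difference |
|---|---|---|---|
| 1% | +98.0% | +49.3% | 48.8 points |
| 10% | +81.8% | +42.9% | 39.0 points |
| 25% | +60.0% | +33.3% | 26.7 points |
| 50% | +33.3% | +20.0% | 13.3 points |

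The difference is below 50 points for every f above zero.

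**3. Power if everyone has the same f.** Simulation: 40,000 trials, 6 per arm, s normal with mean 2.0 or 1.5 and SD 0.30, converted to the ratio and t-tested. The ratio's SD shrinks along with its mean difference. At f = 10% the SDs are about 22 points (control) and 25 points (abatacept); at f = 50% they are about 7 and 10 points. Power is 74% at f = 1% and at f = 10%, and 72% at f = 50%. The smaller point difference alone is almost harmless.

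**4. Power if f differs between participants** (same simulation, other IgE fixed):
- f uniform over 5-50%: 51%
- f log-uniform over 5-50%: 55%
- f log-uniform over 2-50%: 56%
- f log-uniform over 1-10%: 73%

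**5. Power if other IgE varies independently** (f = 10% for all): log-SD of 0.1, 0.2 or 0.3 gives about 61%, 40% or 26%.

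**6. Power if sIgE and other IgE fluctuate together**, as section 3.1 expects. Let 25%, 50% or 75% of the sIgE variance be shared with other IgE (an assumption):
- f log-uniform over 1-10%: about 84%, 95% and above 99%
- f log-uniform over 5-50%: about 64%, 74% and 86%
- f uniform over 5-50%: about 58%, 66% and 78%

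Depending on inputs that the article does not state, power for the ratio can be below, at or above the 74% for sIgE.

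**The case against.** The best defence is section 3.1. The ratio was chosen because sIgE alone carries non-specific variation that wastes power. If that is right, the ratio's SD may be well under 30 and the sIgE calculation may be conservative; step 6 shows this is possible. This part stands, and it rules out any claim that the trial is shown to be less powerful than stated. It does not supply the ratio's SD, however, and section 2.9 makes no such argument. Nor is this detail that an article would leave to an analysis plan: the article does give a power calculation, and it is for another variable.

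Three stronger readings are tempting and not supported.

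- A reader might take the 39, 27 or 13 points as a matching loss of power. Step 3 shows that they are not.
- A reader might infer that a null ratio result could never be told apart from a fall in the denominator. Both components must be measured to form the ratio, so they can be examined. What is true is that section 2.2 lists neither sIgE alone nor total IgE as an outcome.
- A reader might note that a 25% fall in other IgE under abatacept would cancel the effect (1.5/0.75 = 2.0 at small f). The arithmetic is right, but no such figure appears. Section 1.4 mentions reduced IgE production in mice without a size, while sections 1.3 and 1.5 predict an effect selective for peanut-specific cells.

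The gap between 80% and 74% is a separate matter: it comes from the normal approximation and from taking the SD at its stated upper limit.

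**Conclusion.** The point holds as a mismatch between the planning variable and the primary endpoint. The stated 80% power is for the relative change in sIgE and is not demonstrated for the relative change in the ratio. With other IgE unchanged, the planned effect is necessarily smaller than 50 points on the ratio, from about 49 points at the 1% floor set by the entry criteria to 13 points at a baseline share of 50%.

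The effect on power cannot be fixed from the documents. By t-test at 6 per arm and sIgE SD 30, it is negligible with a common or low baseline share (72-74%), substantial with widely spread shares (about 50-56%) or independent denominator variation (26-61%), and favourable if enough of the sIgE variation is shared with total IgE. All of these rest on assumed distributions. The point deserves correction because it bears on how the primary result is read; it does not show that the design fails.

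**What to change.** In section 2.9, state the expected mean change, SD and target difference for the ratio itself, and say whether the 50% suppression threshold refers to the ratio or to sIgE. Restate the t-test power at 6 per arm over a stated range of baseline ratios and of denominator variability, including the shared fluctuation that section 3.1 relies on. This does not require enrolling more participants.

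Report the week-24 relative change in sIgE alone and in total IgE as supportive results, so that a null or positive ratio result can be read against its components.

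The cost is a revised paragraph and two summaries of data already measured. The downside is that the stated power may become less favourable.

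### With the SD at its stated limit of 30 and two-sided testing, the planned t-test has 74% power with 12 evaluable participants, not the 80% that section 2.9 claims

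*Protocol article*

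**What the plan says.** All the sample-size inputs are in section 2.9 of the protocol article.

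- **Test:** "The relative change in specific/total IgE at 24 weeks will be compared between the two groups using Student's" t-test.
- **Planning values:** "we expect the placebo group (OIT alone) to increase their specific IgE levels by 100% with a standard deviation of <30"%.
- **Effect:** "A 50% suppression was deemed clinically significant".
- **Error rates:** "with an alpha risk of 0.05 and a power of 80"%. Whether alpha is one-sided or two-sided is not stated.
- **Size:** "a sample size of 12 participants with a 1:1 randomization ratio would allow the detection of a 50% difference in the increase in sIgE". Enrolment is then raised for dropout: "A total sample size of 14 patients would allow to account for 15% of lost follow-up".

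Section 2.4 adds that the randomization list uses simple randomization. Section 3.2 says that the trial will provide the go/no-go decision for a larger trial. On a negative result, section 3.1 says "If this key finding cannot be replicated in humans, it appears reasonable to assume that the likelihood of replicating the clinical effects would also be" (the sentence ends by calling that likelihood small).

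**The concern.** The normal formula treats the SD as known. With 6 per arm the t-test has only 10 degrees of freedom. Its critical value is 2.228 instead of 1.960, and that gap costs a noticeable amount of power. If 12 came from the normal formula, the 80% does not describe the planned test. The two participants added for dropout would then be needed to reach 80% in the first place.

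The power figure carries weight here. The trial informs whether a larger trial goes ahead, and section 3.1 draws a conclusion from failure to see the effect. How much a negative result says depends on how often the trial would miss a true effect of the size deemed clinically significant.

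**Working it through.** **Inputs (section 2.9).** Difference 50 points: half of a 100% rise is 50 points, so the 50% suppression and the 50% difference agree. SD 30, the only SD figure printed, given there as an upper limit. Alpha 0.05, taken as two-sided. Power 80%. Equal arms. The SD is stated for placebo only; I take it as common to both arms, as Student's t-test does.

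**Step 1: reproduce the plan's figure.** Normal formula per arm:

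n = 2 × (1.960 + 0.842)² × (30/50)² = 5.65, rounded up to 6, so 12 in total.

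This matches the plan. Power by the same approximation: 50 / (30 × √(2/6)) = 2.887; 2.887 − 1.960 = 0.927; Φ(0.927) = 82.3%.

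**Step 2: exact power of the planned test.** Noncentral t with noncentrality 50 / (30 × √(1/n₁ + 1/n₂)) and n₁ + n₂ − 2 degrees of freedom:

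| Evaluable | Noncentrality | df | Critical t | Power |
|---|---|---|---|---|
| 6/6 | 2.887 | 10 | 2.228 | 74.0% |
| 7/6 | 2.996 | 11 | 2.201 | 77.8% |
| 7/7 | 3.118 | 12 | 2.179 | 81.6% |

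At SD 30, 80% is reached with 14 evaluable and not with 13. The chance of a non-significant result under a true 50-point effect at 6/6 is 100 − 74 = 26%, against the 20% implied.

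**Step 3: dependence on the SD, at 6/6.**

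| SD | 25 | 27 | 28 | 29 | 30 |
|---|---|---|---|---|---|
| Power | 87.6% | 82.3% | 79.6% | 76.8% | 74.0% |

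Power is exactly 80% at SD 27.85. With SD held at 30, 80% needs a difference of 53.9 points.

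**Step 4: which SDs lead the normal formula to 12?** It rounds up to 6 per arm when 15.70 × (SD/50)² lies between 5 and 6, that is, SD from about 28.2 to 30.9. Below 28.2 it would have returned 10. If that formula was used with an SD inside the stated limit, t-test power with 12 is therefore below 80% throughout.

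**Step 5: dropout.** 14 × 0.85 = 11.9, and losing 2 of 14 is 14.3%, so the plan expects about 12 evaluable. That is the 74% row at SD 30.

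**Step 6: unequal arms.** Simple randomization of 14 gives exactly 7/7 with probability 3432/16384 = 21%. At SD 30, power is 80.8% at 6/8 and 78.3% at 5/9; with 12 it is 72.8% at 5/7 and 69.0% at 4/8. Averaged over all splits, weighted by their binomial probabilities, power is about 70% with 12 and 78% with 14.

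**The case against.** **The SD is an upper limit.** The plan says below 30, so 74% is the value at the edge of its assumption. With an SD of about 27.8 or less, 12 evaluable do give 80%, and 14 then does hold an allowance for loss. This stands. A reader might infer that the power simply is 74% and that no dropout allowance exists; the document supports that only at or near SD 30. Even so, the claim is made for any SD below 30, and between about 27.8 and 30 it fails. No smaller SD is printed.

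**Sidedness is not stated.** With a one-sided alpha of 0.05, 12 evaluable give 85% at SD 30 and the point falls away. The section does expect an effect in one direction. But an alpha of 0.05 with no qualifier is normally read as two-sided, and Step 1 returns the plan's 12 on the two-sided reading; the one-sided normal formula gives 5 per arm.

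**The abatacept arm may vary less.** If its SD were 15 (an illustration, not a figure from the document), simulated power at 6/6 is about 90%. But the normal formula would then give (30² + 15²) × 7.85 / 50² = 3.5, or 4 per arm, so this is not how the plan reached 12.

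**Is it a miscalculation?** No. The 12 reproduces exactly with a standard formula. The fault is using a large-sample approximation for a t-test with 10 degrees of freedom.

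**The decision rule.** A reader might infer a false no-go risk of 26%. The article sets no criterion that equates a non-significant result with no-go, so 26% is only the chance of non-significance under the Step 2 assumptions. Nor does it give any ground for tabulating power at SDs well above 30.

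**Conclusion.** The point holds in conditional form. For a two-sided Student's t-test at 5%, a 50-point difference and a common SD of 30, 12 evaluable participants in equal arms give 74% power. That is 6 points below the claim, and 80% takes all 14. The statement that 14 absorbs 15% loss fails under the same conditions. Both statements are sound if the SD is about 27.8 or less; the 80% with 12 also holds at SD 30 for a difference of about 54 points. Simple randomization lowers the expected figures further, to about 70% with 12 and 78% with 14 at SD 30.

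A reader might conclude that the trial must enrol more. The documents do not require that: this is a proof-of-concept study, and what is wrong is the stated power.

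**What to change.** Restate the sample-size paragraph in section 2.9 in one of two ways.

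1. Keep SD 30 and give the t-based figures. For example: *With a two-sided 5% Student's t-test, a 50-point difference and a common SD of 30, power is 82% with 14 evaluable participants and 74% with 12, in equal arms.*
2. Keep 80% with 12 evaluable, and state that it rests on an SD of about 27.8 or less, with the basis for that value.

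In either case, say that the test is two-sided and that power was computed from the t distribution. Add that simple randomization does not ensure equal arms, and that averaged over possible splits at SD 30, power is about 70% with 12 and 78% with 14.

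The cost is a change of wording and, under the first option, a less favourable stated power. The number enrolled, the test and the endpoint stay as they are.

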## 3. Discussion

The hypothesis tested in the ATARI study is that abatacept combined with peanut OIT will lead to peanut-specific T and plasma cell suppression and thus increase the rates of clinical remission compared with peanut OIT alone. The hypothesis has strong biological plausibility and is supported by animal models, but it has never been tested in humans.

### 3.1. On the choice of proxy outcome

ATARI is intended as a proof-of-concept study and will likely not be powered to detect differences in clinical remission. Its primary aim is, therefore, to assess differences in a proxy outcome that would be associated with the development of clinical remission.

Based on the choice of proxy outcome, we observed from preclinical studies that abatacept suppresses the initial surge in sIgE with allergen exposure (32). This is assumed to be the consequence of the suppression of peanut sIgE-producing plasma cells and T-cell reactivation and is shown to correlate with the likelihood of clinical remission (9, 17, 18). If this key finding cannot be replicated in humans, it appears reasonable to assume that the likelihood of replicating the clinical effects would also be low.

One risk of using the surge in sIgE as a primary outcome in such a small sample is that we are highly vulnerable to random non-specific variations in total IgE productions, which could have a confounding effect and decrease power. In our own experience of longitudinal testing during peanut OIT or epicutaneous immunotherapy, spontaneous variations in sIgE, even large, are non-clinically significant when they parallel variations in total IgE, hence the choice to measure changes in the sIgE over total IgE ratio as the primary outcome.

Changes in the sIgG4/sIgE ratio are another paraclinical outcome that is often measured during OIT. Since IgG4 production follows the same non-specific expansion/contraction variations as IgE, it is generally a more reliable measure of longitudinal changes in OIT than sIgE alone. However, it is unclear how abatacept will affect sIgG4 production. Based on preclinical data, it is possible that it may suppress the rise in sIgG4, which would complicate interpretation. The sIgG4/sIgE ratio will, therefore, be treated as a secondary outcome.

